#### Data management

Clinical data will be extracted from the hospital’s electronic information systems and dialysis machines. Data will be collected on electronic case record forms (CRF) using web-based Castor EDC [61]. Data will be entered in the data file by an experienced research nurse or research physician. Beforehand, ranges will be defined in the electronic file for all data values to ensure their validity and integrity. Data entry will be checked for 5% of randomly selected CRFs. Patient data will be coded. Analyzing and publication of the results of this study will be performed anonymously.

### Potential consequences of the COVID-19 pandemic

Given the current COVID-19 pandemic and the fact that this study is carried out in a vulnerable population, it is conceivable that the practical implementation of this study will encounter some serious obstacles. As such, interventions requiring direct patient contact and performed solely in the interest of the study, such as cardiac ultrasounds, may be undesirable in times of alarming virus spread.

## Discussion

The HOLLANT study is principally designed to evaluate prospectively whether intradialytic hypotension, as defined under the primary endpoint, is less frequently observed during HV-HDF than during the three other modalities (S-HD, C-HD and LV-HDF). Second, the study aims to assess whether a more favourable intradialytic hemodynamic profile, as measured by various hemodynamic parameters including MAP and DBP, is associated with a lower degree of tissue injury and organ dysfunction, and a better patient tolerance. After all, it is conceivable that a lower blood pressure and/or diminished perfusion is accompanied by tissue injury, organ dysfunction and subjective discomfort, since pre-existing microcirculatory dysfunction is already present in the majority of patients with advanced CKD [17]. In the present study, all these aspects are addressed and, depending on the outcome, analysed for potential interrelationships.

As for the heart, functional changes as observed by STE, will be correlated with intradialytic hemodynamics and with biochemical signs of myocardial damage, such as an increase in the blood levels of CK-MB and release of EVs from cardiomyocytes. Considering the gut, hypoperfusion of the intestinal microcirculation may promote enterocyte injury, loss of the gut-blood-barrier function and increased permeability, thus permitting the intradialytic transfer of mDNA into the circulation. Any increase during dialysis will be correlated with both blood pressure alterations and changes in the inflammatory state, as measured by sCD14 and IL-6R. Tissue injury of various origin, including circulating blood cell elements, the endothelium and cardiomyocytes will be assessed by measuring alterations in the blood levels of EVs. The latter parameters will be correlated with intradialytic hemodynamics as well, and the aforementioned signs of tissue injury, including a rise in CK-MB and mDNA in the blood. Finally, all topics will be related to changes in tympanic body temperature, oxygen and inflammatory status, patient reported temperature sensations and treatment tolerance.

If HV-HDF appears indeed to be associated with a better intradialytic hemodynamic profile and less tissue damage, this will enhance our understanding why HDF is associated with a superior patient outcome and allow the nephrological community to improve this treatment modality even further. If not, the outcome of this study will anyhow teach us if, and to what extent intradialytic hemodynamic instability is associated with tissue injury and patient discomfort, and thus help the medical staff to optimize dialysis treatment in individual cases.

The largest strength of this study is its randomized cross-over design, which prevents that inter-individual differences, such as co-morbidity and prescribed medication, influence the results. An important limitation may be the duration of each dialysis modality, which may be too short to answer all questions. Yet, to minimize patients’ discomfort the underlying protocol was designed in its current form. Since this study is primarily designed to investigate the intradialytic hemodynamics and its consequences on organ and tissue damage between the four most practiced extracorporeal dialysis techniques (S-HD, C-HD, LV-HDF and HV-HDF), potential differences in thermal and sodium balance are not addressed. Another important issue of any study with a cross-over design is the duration of the wash-out period that will most likely prevent carry-over effects of the previous modality. For this study, a wash-out period of 1 week (the first week of every treatment modality) was arbitrarily chosen, since relevant information on this topic is absent.

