### Objectives

The primary objective of the HOLLANT study is to evaluate whether intradialytic hemodynamic stability is better preserved during HV-HDF, by comparing the frequency of intradialytic hypotensive episodes between S-HD, C-HD, LV-HDF and HV-HDF. The main secondary objectives include intradialytic signs of tissue damage as measured by Speckle Tracking Echocardiography (STE), a diversity of laboratory parameters, and patient reported outcome measures (PROMs), such as tolerance and cold (sensations).

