## Methods

### Study design

The HOLLANT study is an open, cross-over, multicenter, intervention RCT in chronic intermittent dialysis patients who will be exposed to four different dialysis modalities: 1) S-HD: HD with a dialysate temperature of 36.5 °C. 2) C-HD: HD with a dialysate temperature 35.5 °C. 3) LV-HDF: HDF with a convection volume of 15 L/1.73 m^2^/session and a dialysate temperature of 36.5 °C. 4) HV-HDF: HDF with a convection volume of ≥23 L/1.73 m^2^/session and a dialysate temperature of 36.5 °C.

After enrollment, participants will be randomized centrally to the four dialysis modalities by using computer randomization software [46]. Randomization occurs in blocks. Enrolled patients will be treated with their usual dialysis modality (either HD or HDF) during the first 2 weeks of the study. Patients who cannot achieve or tolerate a blood flow rate ≥ 350 mL/min during this run-in phase will be excluded before the actual start of the study. Treatment times will be fixed at 4 h per session during the entire conduct of the study. Thereafter, patients start the study-phase and will be treated with S-HD, C-HD, LV-HDF or HV-HDF in a random order. Each dialysis modality will last 2 weeks. The total study duration is 2 (run-in phase) + 8 (study phase) = 10 weeks per patient. An overview of the study is shown in Fig. 1.

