### Statistical methods

Descriptive data will be represented as mean ± standard deviation (SD), median (interquartile range) or number (percentage), when appropriate. The between-treatment number of IDH episodes (based on an intradialytic nadir in SBP as described above) will be analyzed using regression analysis with a Poisson distribution. The mean inter-treatment variability of continuous variables will be calculated using generalized linear mixed effects models with a random intercept, random slope or both, based on the lowest Aikaike’s Information Criterion. A two-sided *p-*value ≤0.05 is considered statistically significant. Statistical evaluations will be performed using IBM SPSS Statistics version 26.0 (Chicago, IL, USA) or RStudio version 1.1.456.

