#### Sample size considerations

We plan to include 40 patients. Loss to follow-up (due to an event) is expected to be about 20%. The number of patients with complete follow-up will be sufficient to detect a 40% lower risk (relative risk of 0.60, α = 0.05, β = 0.80) in the occurrence of the primary endpoint. The power calculation applied was designed for cross-over studies [60].

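### The primary question sets HV-HDF against three modalities, but alpha and power are stated once, for one unnamed contrast, so the two figures do not both hold for the primary claim

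*Protocol article*

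**What the plan says.** The Objectives section frames the primary question as whether haemodynamic stability is better preserved during HV-HDF, "by comparing the frequency of intradialytic hypotensive episodes between S-HD, C-HD, LV-HDF and HV-HDF". The Discussion narrows this to whether hypotension "is less frequently observed during HV-HDF than during the three other modalities (S-HD, C-HD and LV-HDF"), which is three contrasts that share HV-HDF.

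Under Statistical methods, the number of hypotensive episodes "will be analyzed using regression analysis with a Poisson distribution", and one general rule applies: a two-sided p-"value ≤0.05 is considered statistically significant". No contrast is ranked first.

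Under Sample size considerations: "We plan to include 40 patients", with loss to follow-up of about 20%. The number completing is said to be "sufficient to detect a 40% lower risk (relative risk of 0.60, α = 0.05, β = 0.80) in the occurrence of the primary endpoint". The comparator for that relative risk is not named. The value given for β is evidently meant as power of 0.80, and I read it so.

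**The concern.** A three-comparator claim needs a rule that says what counts as success. The article gives none, and its two design figures, alpha 0.05 and 80% power for a relative risk of 0.60, each describe a single comparison.

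The contrasts also answer different scientific questions. The Background reports the view that cooling alone explains the benefit of HDF. The comparison with C-HD bears on that view, the one with LV-HDF bears on convection volume, and the one with S-HD separates neither. Without a named contrast or a success rule, a reader of the results cannot tell which outcome would have confirmed the primary hypothesis, or with what error rate and power.

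**Working it through.** **Inputs from the article.** Four modalities, hence three contrasts with HV-HDF and six pairs in all; two-sided 0.05; relative risk 0.60; power 0.80; 40 patients with 20% loss. "Each dialysis modality will last 2 weeks", at three sessions a week (Table 1), so six sessions per modality, or three if the first week is set aside as wash-out (Discussion).

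**The article's own figure.** 40 × (1 − 0.20) = 32 completers, so the allowance for loss is consistent. The 80% power cannot be reproduced, because the article gives no baseline event rate or within-patient correlation. As a guide, I used a conditional Poisson comparison of two modalities:

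- Share of events expected under HV-HDF: p = 0.60 / 1.60 = 0.375.
- Events needed: [(1.96 × 0.5 + 0.842 × √(0.375 × 0.625)) / (0.5 − 0.375)]² ≈ 123 over the two modalities, of which 123 / 1.6 ≈ 77 fall under the comparator.
- Implied comparator rate: 77 / (32 × 6) ≈ 0.40 episodes per session over six sessions, or 77 / (32 × 3) ≈ 0.80 over three.

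The calculation concerns one pair of modalities only.

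**Reading A: a win in any one contrast counts.** Assume four equal modality effects, estimated with equal variance. Each contrast is z = (HV − other)/√2 on the standardised scale, so any two contrasts correlate at 0.5.

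- At least one |z| > 1.96 among the three: 12.5% by numerical integration (12.6% by simulation). Independent tests would give 1 − 0.95³ = 14.3%.
- At least one false finding in favour of HV-HDF: 6.3%, against 2.5% for one contrast.
- A simulated 32-patient Poisson cross-over with no true difference (three or six sessions, assumed rate 0.1 to 0.4 per session) gave 10.0% to 12.4% and 4.9% to 6.0% respectively. The result does not depend much on the large-sample approximation.

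If Bonferroni were used to repair this (0.05 / 3 = 0.0167 per test), a contrast with 80% power at 0.05 would fall to about 65% (conditional Poisson) or 66% (normal approximation: Φ(2.80 − 2.39)).

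**Reading B: all three contrasts must be won.**

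- False claim when all four modalities are equal: about 0.16%. Worst case, HV-HDF equal to one comparator and far better than the other two: 2.5%. Type I error is controlled.
- Power, if each contrast has 80% (mean z of 1.96 + 0.84 = 2.80): the probability that all three are significant is 61%. Independent contrasts would give 0.80³ = 51%.

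The 61% may be generous. The Background says cooled dialysate alleviates hypotension. If C-HD reduced episodes by an assumed 10% or 20% relative to S-HD, a relative risk of 0.60 against S-HD would become 0.60 / 0.90 = 0.67 or 0.60 / 0.80 = 0.75 against C-HD. One relative risk of 0.60 would then not describe all three comparisons.

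**The case against.** The strongest reply is that this is a condensed article. The full protocol or an analysis plan may fix the contrasts and their order, and the absence of a multiplicity method here is no finding. That stands, and the point does not rest on that absence. It rests on figures the article does state: a three-comparator primary claim, an undivided alpha of 0.05, and power for one relative risk.

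A reader might infer that the primary question carries an unconditional 12% to 20% false-positive risk. The document does not support that, for four reasons:

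- It nowhere says that each contrast is tested separately as its own route to success; the 0.05 sentence is general.
- The Discussion sentence reads naturally as requiring HV-HDF to do better than all three, and then nothing is inflated.
- The 12.5% counts false differences in both directions.
- The 20% figure (20.3% for all six pairs) includes three pairs without HV-HDF, which cannot support the primary hypothesis.

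It could also be said that one Poisson model allows a global test on three degrees of freedom, and the Objectives wording fits that. Such a test is not excluded and would hold 0.05, but it would not show which modality HV-HDF improves on, so the Discussion's question would remain open.

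Finally, making S-HD the primary comparator could demote the C-HD comparison, which the Background treats as important. That is fair, and the choice of contrast and order belongs to the sponsor.

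**Conclusion.** The concern holds in conditional form. The stated alpha and the stated power do not both apply to the three-comparator primary claim. If any one win suffices, the chance of a false difference is about 12.5% and of a false HV-HDF advantage about 6.3%, against 2.5% for one contrast. If all three wins are needed, type I error is sound and the cost is power: about 61% under the favourable assumption of 80% for each contrast.

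These figures assume equal variances and contrasts that share HV-HDF. The 61% also assumes the same power against every comparator, which the article does not claim. The document does not settle which reading is intended, so neither figure can be called the trial's actual error rate or power. This should be corrected, and before the data are analysed: the article reports 25 of 40 patients included in an open trial.

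**What to change.** Before analysis, state one of the following in the protocol or analysis plan.

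(a) Name one primary contrast, for example HV-HDF versus S-HD, at two-sided 0.05, and tie the relative risk of 0.60 and the 80% power to it. Test the other two HV-HDF contrasts in a fixed order at 0.05, each only if the previous one is significant. The sponsor chooses the primary contrast and the order. Report the remaining pairs descriptively with confidence intervals.

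(b) State that HV-HDF must be significantly better in all three contrasts, each at two-sided 0.05, and restate the power for that joint claim, with the relative risk assumed against each comparator.

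Either takes a sentence or two. Under (a) the first contrast keeps its full alpha and needs no more patients on account of multiplicity, but later contrasts lose confirmatory status if an earlier one fails. Under (b) the wording of the Discussion is kept, but the stated power will be lower than 80%, about 61% on the assumptions above.

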## Background

Despite the use of high permeable dialyzers, which combine diffusive with convective transport, the clinical outcome of hemodialysis (HD) patients remains poor. In online post-dilution hemodiafiltration (HDF), diffusion is by and large similar to HD, while the amount of convective transport is considerable higher. Recently, four randomized controlled trials (RCT) have been published which compared HD with HDF [1–4]. Although the results of the individual studies were inconclusive, a recent meta-analysis on individual participant data (IPD) showed a superior outcome for patients treated with HDF (all-cause mortality HR 0.86 [95% CI: 0.75; 0.99]). The largest mortality reduction was obtained in patients receiving the highest convection volume (high-volume HDF [HV-HDF] > 23 L/1.73 m^2^/session: all-cause mortality HR 0.78 [95% CI: 0.62; 0.98], if compared to HD) [5].

Nonetheless, it is still unclear why HV-HDF is associated with an improved survival [6]. On theoretical grounds, both the enhanced removal of middle molecular weight uremic retention products and a superior bio-incompatibility (BI) profile [7], including less inflammation [8, 9] and less dialysis-induced hypoxia [10, 11], may play an important role. Moreover, since treatment with HDF has been associated with a lower incidence of intradialytic hypotension (IDH) than standard HD [12–15], in which an altered sodium removal during HDF may play a role [16], a lesser amount of dialysis-induced tissue damage may also contribute to the beneficial effect of HDF on survival.

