#### Blood sampling

Blood sampling will be performed in the last session of each dialysis modality, after the long interdialytic interval (see Fig. 1). Blood samples will be drawn from the arterial line of the extracorporeal circuit (ECC) before treatment (but after administration of LMWH) and after 4 h of treatment (see Table 2). After processing, all blood samples will be stored at − 80 °C until assessment in the central laboratory of the hospital of the Amsterdam University Medical Centers.

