#### Markers of inflammation, cardiac- and endothelial damage and FGF23

Soluble CD14 (sCD14), interleukin-6 receptor (IL-6R), high sensitive C-reactive protein (hs-CRP), creatine kinase myocardial band (CK-MB), soluble vascular intercellular cell adhesion molecule 1 (sv-ICAM-1), and fibroblast growth factor 23 C-terminal (FGF23 C-term) will be assessed in EDTA or heparin plasma samples after being placed on ice and centrifuged within 30 min, at 1800 g for 10 min.

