#### Secondary endpoints

Secondary endpoints include: 1) intradialytic LV chamber quantification and deformation (longitudinal function with speckle tracking) and LV diastolic function; 2) the intradialytic hemodynamic profile of SBP, DBP, MAP and PP; 3) organ and tissue damage, such as the release of specific cellular components; and 4) patient-reported symptoms and thermal perceptions during each modality.

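### For soluble damage markers that cross the membrane, a smaller rise under HV-HDF cannot be told apart from greater removal, and the article's injury inference carries no such caveat

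*Protocol article*

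**What the plan says.** **Sampling.** Blood is taken from the arterial line in the last session of each modality, "before treatment (but after administration of LMWH) and after 4 h of treatment" (Blood sampling).

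**Markers.** The soluble panel is "Soluble CD14 (sCD14), interleukin-6 receptor (IL-6R), high sensitive C-reactive protein (hs-CRP), creatine kinase myocardial band (CK-MB"), sv-ICAM-1 and C-terminal FGF23 (Markers of inflammation, cardiac- and endothelial damage and FGF23). Table 2 files CK-MB under cardiac damage, sv-ICAM-1 under endothelial damage and sCD14 under gut ischemia. It files hs-CRP and IL-6R under inflammation and FGF23 as a special biomarker.

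**How they are read.** The third secondary endpoint is "organ and tissue damage, such as the release of specific cellular components". The Discussion refers to "biochemical signs of myocardial damage, such as an increase in the blood levels of CK-MB and release of EVs from cardiomyocytes". It also says that injury of various origin "will be assessed by measuring alterations in the blood levels of EVs".

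**Removal.** The Background describes convective transport as considerably higher in HDF than in HD. Among the possible reasons for better survival it names "the enhanced removal of middle molecular weight uremic retention products". Dialysis modalities sets the convection target at 15 L for LV-HDF and 25 L (at least 23 L) for HV-HDF. All arms use high-flux dialyzers (Dialyzers).

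**Conclusion drawn.** The Discussion continues from "If HV-HDF appears indeed to be associated with a better intradialytic hemodynamic profile and less tissue damage" to a better understanding of why HDF is associated with superior outcome. Its limitations cover period length, thermal and sodium balance, and wash-out between periods. Removal of the markers is not among them.

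**The concern.** A blood level at 4 h reflects what the tissue released and what the dialyzer took out. Both happen between the two samples, so using the change from the pre-dialysis value does not separate them. If removal were equal in all arms it would cancel in the comparison. Here it is part of the intervention and rises from HD through LV-HDF to HV-HDF.

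The Background offers enhanced solute removal and less tissue damage as two separate explanations of the HDF survival benefit. For a filterable marker, the planned blood measurement cannot distinguish them. The bias would fall on the main contrast, HV-HDF against the other three modalities, in the direction the trial hopes to see. The cross-over design cannot help, because the treatment itself causes the difference.

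The planned correlations of marker rises with hemodynamics are exposed too. Modality drives removal and is hypothesized to drive blood pressure, so pooled data could link stable pressure with lower marker levels even if release did not differ.

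**Working it through.** The article gives no figure on this point to reproduce. The calculation below shows direction and possible size only.

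**Inputs from the article:** convection Q = 25 L (HV-HDF) and 15 L (LV-HDF).

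**Assumptions, not in the article:** Q = 2.5 L net ultrafiltration in HD; sieving coefficient S from 0.01 to 0.10; distribution volume Vd = 3.5 L (about plasma volume) or 12 L; one compartment; no diffusion, internal filtration or hemoconcentration.

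**Step 1. Level already present before the session, no release.** The fraction left at 4 h is exp(−S × Q / Vd). The shortfall in HV-HDF relative to HD is

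1 − exp(−S × (25 − 2.5) / Vd) = 1 − exp(−S × 22.5 / Vd).

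Example, S = 0.05 and Vd = 3.5 L: 1 − exp(−0.3214) = 27.5%.

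**Step 2. Marker released evenly over the 4 h.** Released material is exposed to removal for only part of the session. With k = S × Q / Vd, the fraction of the released amount still present at 4 h is f(k) = (1 − exp(−k)) / k. The shortfall is 1 − f(k in HV-HDF) / f(k in HD).

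Example, S = 0.10 and Vd = 3.5 L: k is 0.7143 in HV-HDF and 0.0714 in HD, so f is 0.7146 and 0.9651, and the shortfall is 1 − 0.7146 / 0.9651 = 26.0%.

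**Results, HV-HDF lower than HD by:**

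| Vd | S | Pre-existing level | Released component |
|---|---|---|---|
| 3.5 L | 0.01 | 6.2% | 3.1% |
| 3.5 L | 0.05 | 27.5% | 14.4% |
| 3.5 L | 0.10 | 47.4% | 26.0% |
| 12 L | 0.01 | 1.9% | 0.9% |
| 12 L | 0.05 | 8.9% | 4.5% |
| 12 L | 0.10 | 17.1% | 8.8% |
| any | 0 | 0% | 0% |

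At S = 0.001 the pre-existing level differs by only 0.6% (3.5 L) or 0.2% (12 L).

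**Step 3. HV-HDF against LV-HDF.** The convection difference is 10 L, so the Step 1 shortfall is 1 − exp(−S × 10 / Vd). At S = 0.10 this gives 24.9% (3.5 L) or 8.0% (12 L).

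**Step 4. Dependence on Vd.** Take a level 10% lower in HV-HDF than in HD. Wash-out of a pre-existing level explains all of it at S = −ln(0.9) × Vd / 22.5. That is 0.016 for Vd = 3.5 L and 0.056 for Vd = 12 L, a ratio of 12 / 3.5 = 3.4. A break-even sieving coefficient therefore means little unless the distribution volume is stated with it.

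**The case against.** The case against has five parts.

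- **No marker is shown to be filterable.** The article gives no molecular size or sieving coefficient, and its remark on middle molecules does not mention these proteins. This stands. The bias is possible for each marker and demonstrated for none.
- **Not every protein in the panel is read as injury.** A reader might infer that any fall in a measured protein would be counted as less damage. The text does not support that: C-terminal FGF23 is nowhere read as injury, and IL-6R is read as inflammation. The point covers CK-MB, sv-ICAM-1, and sCD14 as a gut-ischemia marker, which the Discussion also uses for inflammatory state.
- **The injury claim does not rest on soluble proteins alone.** EVs already carry part of it. STE before, at 1 h and at 3 h is not altered by removal of a marker from blood. A reader might infer that HV-HDF could be declared less injurious through wash-out alone. The article sets no such rule, and its concluding sentence is conditional and also requires a better hemodynamic profile. This limits the consequence. However, the section on the COVID-19 pandemic warns that cardiac ultrasounds may become undesirable, which would shift weight to the blood markers.
- **The larger percentages can be misread.** A reader might take 6%, 27% and 47% as the difference under identical tissue release. They describe wash-out of a level already present, with no release. For evenly released marker the gap is about half. The model also leaves out diffusion and internal filtration.
- **Marker interpretation may sit in the full protocol or analysis plan.** That is so, and the absence of a correction is not the complaint. The article states its reading of the markers and the inference drawn from it without this condition.

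**Conclusion.** The point holds as a limit on interpretation. For a soluble damage marker that passes the membrane, a smaller pre-to-4 h rise under HV-HDF cannot be distinguished from greater clearance, and the possible bias favours the trial's hypothesis.

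The size cannot be fixed from the article. It is nil for a marker that does not pass. Under the stated assumptions it runs from about 2% to 47% for a pre-existing level and about 1% to 26% for marker released evenly in the session, HV-HDF against HD.

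Only secondary endpoints are affected. The SBP-nadir primary endpoint, the hemodynamic profile and the patient-reported outcomes are not measured through these markers.

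**What to change.** 1. Report between-modality changes in CK-MB, sv-ICAM-1 and sCD14 as net of removal, and say so wherever they are described as damage.
2. Add a sensitivity analysis that corrects the 4 h level using the recorded convection volume in the HDF arms and weight loss in the HD arms. Vary both the sieving coefficient (including 0) and the distribution volume, and report the combinations at which the HV-HDF difference disappears. Show the pre-existing and released components separately.
3. Rest any claim of less tissue damage under HV-HDF primarily on STE and EVs, with filterable soluble markers as supportive only. The article does not give EV size, so state as an assumption that EVs are too large to pass. Microbial DNA should not be dropped without a stated reason.
4. Add marker removal to the limitations.

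The cost is wording and a small calculation on data already being collected, with no new sampling. The downside is a weaker claim from the soluble markers.
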